### Trial oversight

This is a single-center investigator-initiated trial coordinated by the Department of Tuina, Hangzhou Hospital of Traditional Chinese Medicine. The study team will be responsible for participant screening, recruitment, intervention delivery, outcome assessment, data collection and study coordination. The principal investigator will have overall responsibility for trial conduct and protocol compliance. No separate steering committee or endpoint adjudication committee has been established because this is a single-center trial with a modest sample size and low-risk physical interventions. Data management and quality control will be conducted by the study investigators according to predefined study procedures.

#### Trial monitoring.

Trial conduct will be monitored by the study investigators throughout the recruitment, intervention, follow-up, and data-management phases. Screening logs, recruitment progress, intervention adherence records, case report forms, protocol deviations, and adverse events will be reviewed at regular intervals, at least once every month during active recruitment and treatment. Source data checks and review of data completeness and consistency will be performed periodically by designated members of the study team who are not responsible for the participant’s routine treatment on the day of review, where feasible. Important protocol deviations, safety concerns, and data-quality issues will be documented and discussed by the study team, and corrective actions will be implemented when needed. No separate external trial monitoring committee has been established because this is a single-center study of low-risk physical interventions.

#### Safety monitoring.

All adverse events will be recorded during the intervention and follow-up periods. Adverse events will be assessed systematically at each treatment session and follow-up contact and will be classified by severity and relatedness to the intervention. Expected mild events may include temporary neck soreness, brief discomfort during exercise, or transient dizziness. The allocated intervention will be stopped if a participant develops intolerable symptoms, marked worsening of neurological signs, a serious adverse event or another condition requiring alternative medical management. Serious adverse events will be reported promptly to the ethics committee in accordance with local requirements.

#### Data monitoring committee.

A separate data monitoring committee will not be established for this trial because this is a single-center study of low-risk physical interventions with a modest sample size and no planned interim efficacy analyses. Trial conduct and safety oversight will instead be managed by the study investigators in accordance with the protocol and institutional requirements.

#### Interim analyses and stopping guidelines.

No formal interim efficacy analyses are planned because this is a single-center trial with a modest sample size and a relatively short intervention period. The study team will review safety events throughout the trial. The principal investigator will have access to accumulating safety information and will make the final decision on trial suspension or termination if there are significant safety concerns, major protocol problems, or ethical reasons requiring early discontinuation. Serious adverse events will be reported promptly to the ethics committee.

### Sample size

The sample size was calculated based on the primary outcome, namely affected-side sternocleidomastoid stiffness at week 4. Because directly comparable shear-wave elastography data from children with AARS were unavailable, the assumptions were informed by preliminary observations and published studies of cervical muscle stiffness measured using shear-wave elastography [25,26]. A target between-group difference of 6.5 kPa and a common standard deviation of 9.0 kPa were assumed, corresponding to a standardized effect size of approximately 0.72. With a two-sided significance level of 0.05, 80% power, and a 1:1 allocation ratio, 31 participants were required in each group. Allowing for approximately 10% attrition or unavailable week-4 primary outcome data, the final target sample size was set at 70 participants, with 35 participants in each group.

Given the limited pediatric AARS-specific elastography evidence available when the trial was designed, these assumptions should be interpreted cautiously. The trial is designed to test the prespecified primary hypothesis and will also provide estimates of treatment effects and outcome variability for future larger multicenter studies.

### Data collection, management and quality control

Trained investigators will record study data in standardized case report forms and then enter them into a password-protected electronic database. Each participant will be assigned a unique study identification number, and personally identifiable information will be stored separately from study data. Key outcome data will be entered independently by two trained staff members. Discrepancies will be checked against the original case report forms and source documents and resolved before database lock. Range checks and logical consistency checks will be performed regularly for demographic variables, eligibility criteria, treatment attendance, outcome scores, ultrasound values, adverse events, protocol deviations, and follow-up data. Data queries will be generated when missing, inconsistent, or implausible values are identified. These queries will be reviewed and resolved by authorized study personnel using source documents whenever possible. All corrections will be documented. Only authorized study staff will have access to the final dataset. Regular data-quality checks will be performed throughout recruitment, treatment, follow-up, and database preparation.

### Retention strategies

To minimize missing data and loss to follow-up, several retention strategies will be implemented. Appointment times will be scheduled flexibly according to the availability of the child and legal guardian. Guardians will receive reminders before treatment and assessment visits by telephone or electronic message. Missed visits will be followed up within 24–48 hours, and outcome assessments will be rescheduled as soon as possible within the prespecified assessment window. The study team will maintain regular contact with guardians during the intervention and follow-up periods to encourage treatment attendance, adherence to study instructions, and completion of outcome assessments. Reasons for missed treatment sessions, missed assessments, withdrawal, or loss to follow-up will be recorded whenever possible.

### Confidentiality

Personal information obtained during screening and trial participation will be collected only by authorized study staff and will be handled in a confidential manner. Participants will be assigned unique study identification numbers, and identifiable information will be stored separately from research data in secure files or password-protected electronic systems with restricted access. Paper records will be kept in locked storage areas at the study site, and electronic data will be stored on secure institutional systems. No directly identifiable participant information will be used in reports, presentations, or publications. Access to identifiable data will be limited to personnel who require such access for trial conduct, oversight, or regulatory purposes. After trial completion, study records will be retained and managed in accordance with applicable institutional and regulatory requirements.

### Missing data

Missing data are expected to be limited, with an anticipated missing data rate of approximately 10%, consistent with the dropout allowance used in the sample size calculation. When missing or inconsistent data are identified, the study team will first verify the original case report forms and source documents. Data queries will be generated and resolved by trained study personnel before database lock. If data remain missing, the reason for missingness will be documented whenever possible, including withdrawal, missed assessment, poor ultrasound image quality, inability to complete the assessment, receipt of prohibited co-interventions, or loss to follow-up.

The primary analysis will follow the intention-to-treat principle, with participants analyzed according to their originally assigned groups. The primary ANCOVA will use participants with available baseline and week-4 primary outcome data. If missing primary outcome data are considered likely to influence the results, multiple imputation under the missing-at-random assumption will be performed as a sensitivity analysis. Linear mixed-effects models for repeated secondary outcomes will use all available data under the missing-at-random assumption. No imputation will be performed for adverse events; these will be summarized based on observed data.

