#### Protocol clarification.

The original ethics-approved clinical trial protocol in Chinese is provided as S1 File, and its complete English translation is provided as S2 File. It specified a single-center randomized controlled design, 70 participants, joint mobilization as the control intervention, joint mobilization combined with cervical resistance training as the intervention, a 4-week treatment period with 3 sessions per week, and follow-up at 3 and 6 months after treatment. In this manuscript, several reporting clarifications were made to meet clinical trial reporting standards. Affected-side sternocleidomastoid stiffness at week 4 was specified as the primary ultrasound-based endpoint based on the SWE-based cervical muscle elasticity outcome listed in the original protocol. The ultrasound analysis in this manuscript focuses on the sternocleidomastoid and upper trapezius muscles because these muscles are more directly related to torticollis presentation and can be measured more reproducibly in children. FPS-R and Pediatric NDI were used as pediatric-adapted measures of pain and neck disability, and week 2 was added as a non-primary interim assessment point to describe short-term changes during treatment. This additional assessment will not be used for the primary efficacy conclusion. These clarifications did not change the intervention framework, sample size, or overall study objective.

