#### Shear-wave elastography parameters.

SWE will assess the bilateral sternocleidomastoid and upper trapezius muscles at baseline, week 2, and week 4. These data will describe broader changes in cervical muscle mechanics during recovery and will support the interpretation of the primary outcome [30,31].

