### Statistical analysis

Statistical analyses will be performed using SPSS version 22.0. Continuous variables will be presented as mean ± standard deviation when normally distributed or as median (interquartile range) when not normally distributed. Categorical variables will be presented as frequencies and percentages.

The statistical analysis plan was refined in this manuscript to meet randomized trial reporting standards. The original ethics-approved protocol specified descriptive statistics and pre-post comparisons. The manuscript further specifies baseline-adjusted between-group analysis for the primary endpoint and repeated-measures models for longitudinal outcomes.

The intention-to-treat population will include all randomized participants, who will be analyzed according to their originally assigned groups. The primary ANCOVA will be based on participants with available baseline and week-4 primary outcome data. Multiple imputation under the missing-at-random assumption will be performed as a sensitivity analysis if missing primary outcome data are considered likely to influence the results.

The primary outcome will be analyzed with analysis of covariance, with affected-side sternocleidomastoid stiffness at week 4 as the dependent variable, treatment group as the fixed factor, and baseline affected-side sternocleidomastoid stiffness as the covariate. Adjusted between-group differences with 95% confidence intervals will be reported. To avoid overfitting given the modest sample size, additional covariate adjustment will be limited to prespecified clinically relevant variables. A supplementary adjusted model may include age, sex, baseline symptom duration, and baseline pain intensity, if model assumptions and data completeness permit. These analyses will be considered supportive of the primary baseline-adjusted analysis.

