### Sensitivity analyses

The intention-to-treat analysis will be considered the primary analysis. A per-protocol analysis will be performed as a sensitivity analysis to assess the robustness of the primary findings. The per-protocol population will include participants who complete the week-4 primary outcome assessment, receive at least 80% of the assigned treatment sessions, have no major protocol deviations, and do not receive prohibited co-interventions during the intervention period. Sensitivity will be evaluated by comparing the direction, magnitude, and 95% confidence intervals of the treatment effect between the intention-to-treat and per-protocol analyses. If the results are consistent across these analyses, the findings will be considered robust. If meaningful discrepancies are observed, the potential influence of adherence, missing data, and protocol deviations will be examined and reported.

All tests will be two-sided. A P value <0.05 will be considered statistically significant for the primary analysis. Secondary analyses will be interpreted as supportive and exploratory, with multiplicity-adjusted P values reported where appropriate.

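### The primary analysis called intention-to-treat leaves out every child without a week-4 scan, and the stated robustness rule cannot detect any bias this causes

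*Protocol article*

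**What the plan says.** All references are to the protocol article.

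- **Label.** Under Missing data: "The primary analysis will follow the intention-to-treat principle, with participants analyzed according to their originally assigned groups". Under Statistical analysis: "The intention-to-treat population will include all randomized participants, who will be analyzed according to their originally assigned groups". Sensitivity analyses then names the intention-to-treat analysis as primary.
- **Analysis set.** Under Missing data: "The primary ANCOVA will use participants with available baseline and week-4 primary outcome data". Statistical analysis repeats the restriction. The model has "treatment group as the fixed factor, and baseline affected-side sternocleidomastoid stiffness as the covariate".
- **Imputation.** Multiple imputation under missing at random is a sensitivity analysis, done on a condition: "If missing primary outcome data are considered likely to influence the results". The article names neither a criterion nor who decides.
- **Robustness rule.** Sensitivity analyses compares the intention-to-treat and per-protocol results: "If the results are consistent across these analyses, the findings will be considered robust". The per-protocol set requires a completed week-4 primary assessment, among other conditions. The influence of missing data is examined only if the two analyses differ meaningfully.
- **Week 2.** "SWE will assess the bilateral sternocleidomastoid and upper trapezius muscles at baseline, week 2, and week 4". Protocol clarification adds: "This additional assessment will not be used for the primary efficacy conclusion".

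**The concern.** Two things do not fit together. The population is defined as everyone randomized, but the analysis carrying that label contains only children scanned at week 4. The label is therefore stronger than the analysis.

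The robustness rule matters more. A child without a week-4 scan is outside the primary ANCOVA and, by definition, outside the per-protocol set. Comparing the two cannot show what those children would have contributed. Yet agreement earns the verdict of robustness, and disagreement between these same two sets is what triggers a look at missing data. The one analysis that could speak to the missing children, multiple imputation, may never be run.

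Informative missingness is plausible on the article's own terms. Withdrawal criteria include clinical deterioration and inability to continue. Families and therapists know the allocation. Missing data lists prohibited co-interventions among the reasons a value may be absent. The report could then claim both intention-to-treat and robustness without the plan supporting either claim as regards missing data.

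**Working it through.** **1. The plan's own figures.** From Sample size: difference 6.5 kPa, SD 9.0 kPa, two-sided alpha 0.05, power 80%, 1:1 allocation.

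n per arm = 2 × [9.0 × (1.960 + 0.842) / 6.5]² = 30.1, rounded up to 31. With 10% loss: 31 / 0.9 = 34.4, rounded up to 35, so 70 in total. Both figures reproduce.

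**2. Who is analyzed.** 70 × 0.90 = 63 children in the primary ANCOVA, against 70 in the defined population. About 7 are left out.

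**3. What the robustness comparison can see.** The per-protocol set is a subset of the children scanned at week 4, so the children without that scan are in neither analysis. If the subset is a random 80% to 90% of completers (assumed), the two estimates correlate at about √0.80 = 0.89 to √0.90 = 0.95. Agreement is largely built in.

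**4. How bias arises.** In one arm, full mean = observed mean + m × gap, where m is the missing fraction and gap is the difference between missing and observed children after baseline adjustment. With m = 0.10 in one arm only, gaps of 3, 6.5 and 9 kPa shift the contrast by 0.30, 0.65 and 0.90 kPa. Equal fractions and equal gaps in both arms cancel; opposite gaps add. If missingness depends only on arm and baseline, the adjusted gap is zero, provided the ANCOVA is correctly specified.

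**5. Simulation.** The target difference and SD are the article's. Everything else is assumed: correlations baseline/week 2 of 0.5 to 0.6, baseline/week 4 of 0.4 to 0.5 and week 2/week 4 of 0.6 to 0.8; a week-2 effect half the week-4 effect; and week-2 scans complete. Rows 1 to 3 use 35 per arm and 6,000 runs per setting. Rows 4 and 5 come from separate large-sample simulations (SD 9, baseline/week 4 correlation 0.5, week 2/week 4 correlation 0.7). The comparison estimate uses week 2 and keeps every randomized child. Biases are in kPa.

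| Missingness at week 4 | Complete-case bias, true effect 6.5 | Complete-case bias, true effect 0 | Error using week 2 |
|---|---|---|---|
| 1. 10% in each arm, completely at random | 0.04 or less | 0.06 or less | 0.06 or less |
| 2. About 13% intervention (mostly the stiffest at week 2), 5% control at random | benefit overstated by 0.56 to 0.72 | 0.56 to 0.71 | 0.03 or less |
| 3. About 10% in each arm: stiffest lost in intervention, least stiff lost in control | overstated by 0.99 to 1.16 | 0.94 to 1.16 | 0.07 or less |
| 4. 14.6% control, 3.3% intervention, rising with week-2 stiffness | understated by 0.46 (6.04 against 6.5) | 0.49 | 0.04 or less |
| 5. Row 4 with the arms swapped | overstated by 0.41 to 0.53 (6.91 to 7.03) | as row 4, sign reversed | 0.01 or less |

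The largest value is 1.16 / 6.5 = 18% of the target. A milder split of about 12% against 5% to 7% gave about 0.2 kPa. A further run of the row 3 pattern gave about 0.8 kPa.

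**6. Effect on the test.** With 63 children and baseline correlation 0.5, SE = 9 × √(1 − 0.25) × √(2 / 31.5) = 1.96 kPa. A bias of 0.49 kPa is 0.25 SE, and type I error becomes Φ(−1.71) + Φ(−2.21) = 5.7%. A bias of 1.16 kPa with the simulated SE of 1.94 is 0.60 SE, giving Φ(−1.36) + Φ(−2.56), about 9%.

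**7. Precision.** With data missing completely at random, using week 2 lowers the SE by only about 1% to 3%. The gain is protection against bias, not power.

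**The case against.** The restriction to observed cases is not hidden: two sections state it, and Missing data explains the intention-to-treat principle as analysis by assigned group. Baseline-adjusted ANCOVA with imputation as a sensitivity analysis is a recognised approach at about 10% missing. An imputation model and its trigger are commonly left to a statistical analysis plan, and the article promises one before database lock. The simulated bias is modest, rests on assumed inputs, and can run against the intervention. All of this stands. It makes the label a matter of wording and lowers the severity. It does not rescue the robustness rule, which the article already fixes and which cannot do what it claims.

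A reader might infer more than the text supports:

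- **That week 2 is barred from handling missing values.** The primary ANCOVA omits it, but no section excludes it from the imputation model. Protocol clarification only keeps it out of the primary efficacy conclusion.
- **That imputation will be chosen after seeing unblinded results.** The article does not say when or by whom the judgement is made, and analysts are to stay blinded until the main analysis where possible. What is shown is a missing criterion.
- **That week 2 is available for every child.** It is scheduled for all, but early dropouts may lack both scans, so the near-zero errors in the last column of the table are optimistic.
- **That nothing else touches missing data.** The mixed models for bilateral sternocleidomastoid stiffness use all available data and may cover the affected side. They are secondary, exploratory and outside the robustness rule.

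**Conclusion.** The point holds and should be fixed. The primary analysis is an observed-case analysis of about 63 of 70 children under an intention-to-treat label. The rule for calling findings robust gives no information about the children left out, and the only named check that would do so on the primary result is conditional without a criterion.

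The size is modest: about 0 to 1.2 kPa against 6.5 kPa, in either direction. It reaches the upper end only if the two arms lose opposite kinds of children. It is about zero if missingness depends only on arm and baseline. These figures rest on assumed correlations and dropout patterns that the article does not give. Power is not the issue, because the 10% allowance covers the expected loss. The documents do not support a claim that the trial is biased towards the intervention, or that the ANCOVA must be replaced.

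**What to change.** 1. Keep the baseline-adjusted ANCOVA and describe it as an analysis of observed cases by assigned group. Align the wording in Missing data, Statistical analysis and Sensitivity analyses.
2. Always run multiple imputation by arm on all 70 randomized children, with baseline and, where available, week-2 affected-side stiffness in the imputation model. Remove the condition.
3. State that week 2 serves only to inform missing week-4 values, which respects Protocol clarification.
4. Reword Sensitivity analyses so that robustness to missing data is judged from the imputed analysis, and agreement with per-protocol speaks only to adherence and protocol deviations.

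A delta-adjusted (not-at-random) analysis, or a mixed model as the primary analysis, is optional.

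The cost is wording and some programming, with no new data and no change to the 70 children. Recruitment is planned to run to 31/10/2026 and the statistical analysis plan is described as still to be finalized, so the change can be made before database lock. The downside is that the imputed result may be less favourable than the observed-case one.

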### Statistical analysis

Statistical analyses will be performed using SPSS version 22.0. Continuous variables will be presented as mean ± standard deviation when normally distributed or as median (interquartile range) when not normally distributed. Categorical variables will be presented as frequencies and percentages.

The statistical analysis plan was refined in this manuscript to meet randomized trial reporting standards. The original ethics-approved protocol specified descriptive statistics and pre-post comparisons. The manuscript further specifies baseline-adjusted between-group analysis for the primary endpoint and repeated-measures models for longitudinal outcomes.

The intention-to-treat population will include all randomized participants, who will be analyzed according to their originally assigned groups. The primary ANCOVA will be based on participants with available baseline and week-4 primary outcome data. Multiple imputation under the missing-at-random assumption will be performed as a sensitivity analysis if missing primary outcome data are considered likely to influence the results.

The primary outcome will be analyzed with analysis of covariance, with affected-side sternocleidomastoid stiffness at week 4 as the dependent variable, treatment group as the fixed factor, and baseline affected-side sternocleidomastoid stiffness as the covariate. Adjusted between-group differences with 95% confidence intervals will be reported. To avoid overfitting given the modest sample size, additional covariate adjustment will be limited to prespecified clinically relevant variables. A supplementary adjusted model may include age, sex, baseline symptom duration, and baseline pain intensity, if model assumptions and data completeness permit. These analyses will be considered supportive of the primary baseline-adjusted analysis.

Repeated secondary outcomes will be analyzed according to their scheduled assessment time points. SWE parameters and cervical rotation range of motion will be assessed at baseline, week 2, and week 4. Pain intensity and cervical disability will be assessed at baseline, week 2, week 4, and at 3 and 6 months after treatment. Recurrence-related outcomes will be assessed at 3 and 6 months after treatment. Linear mixed-effects models will be used for repeated outcomes, with terms for group, time, and the group-by-time interaction, where appropriate. The overall effectiveness rate at week 4 will be compared between groups using the chi-square test or Fisher’s exact test, as appropriate.

The primary outcome will be tested at a two-sided significance level of 0.05 without adjustment for multiplicity. Secondary outcomes will be interpreted as supportive and exploratory. To address potential multiple comparison issues across secondary outcomes, adjusted P values using the Holm-Bonferroni method will be reported where appropriate, together with effect estimates and 95% confidence intervals. Interpretation of secondary outcomes will emphasize the magnitude and precision of treatment effects rather than statistical significance alone.

Model assumptions will be assessed before final interpretation of the primary and secondary analyses. For the ANCOVA model, residual distribution, homogeneity of variance, linearity between the baseline covariate and the week-4 outcome, and influential observations will be examined using residual plots and appropriate diagnostic procedures. For linear mixed-effects models, residual distribution, variance structure, and model convergence will be assessed. If substantial deviations from model assumptions are observed, data transformation or robust standard errors will be considered where appropriate. For the primary outcome, a rank-based ANCOVA adjusted for the baseline value of the primary outcome will be used as a non-parametric sensitivity analysis if the assumptions of the standard ANCOVA are not met. For repeated secondary outcomes, if the assumptions of linear mixed-effects models are seriously violated, transformed outcome models, robust variance estimation, or rank-based repeated-measures approaches will be considered as sensitivity analyses. These alternative analyses will be interpreted as sensitivity analyses, while the prespecified ANCOVA and linear mixed-effects models will remain the primary analytical framework.

Binary recurrence-related outcomes at the 3- and 6-month follow-up visits will be compared using the chi-square test or Fisher’s exact test, as appropriate. Additional exploratory analyses may be conducted for other ultrasound-derived measures according to the final data structure and distribution.

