### Randomization and allocation concealment

Participants will be randomly assigned in a 1:1 ratio to the intervention group or the control group. The random allocation sequence will be generated by an independent statistician using computer-generated block randomization. Group assignments will be placed in sequentially numbered, opaque, sealed envelopes prepared by personnel not involved in recruitment, treatment or outcome assessment. After baseline assessment and confirmation of eligibility, the next envelope in sequence will be opened to reveal treatment allocation.

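### Adding age as one continuous term to the primary ANCOVA would be a cheap gain in precision and robustness in a trial of ages 2–18; the present baseline-only analysis is valid

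*Protocol article*

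**What the plan says.** The Statistical analysis section of the protocol article fixes the primary model for week-4 affected-side stiffness, with "treatment group as the fixed factor, and baseline affected-side sternocleidomastoid stiffness as the covariate". It then says that, because the sample is modest and overfitting is to be avoided, further adjustment will be confined to prespecified, clinically relevant variables. It continues: "A supplementary adjusted model may include age, sex, baseline symptom duration, and baseline pain intensity, if model assumptions and data completeness permit". That model is described as supportive.

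The Inclusion criteria admit children from 2 to 18 years. Under Randomization and allocation concealment, "The random allocation sequence will be generated by an independent statistician using computer-generated block randomization"; neither that section nor Implementation names a stratification factor. The Sample size section states: "A target between-group difference of 6.5 kPa and a common standard deviation of 9.0 kPa were assumed", and "With a two-sided significance level of 0.05, 80% power, and a 1:1 allocation ratio, 31 participants were required in each group".

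**The concern.** The plan treats age as clinically relevant and has it for every randomized child, since eligibility cannot be confirmed without it. Nothing described in the randomization balances age across a 16-year range. If age predicts week-4 stiffness beyond what baseline stiffness already tells us, leaving it out of the primary model gives a wider confidence interval than necessary. It also leaves the estimate exposed to whatever age difference arises by chance in this trial.

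The reason given for few covariates is overfitting. That is a fair caution about four extra covariates in about 62 evaluable children, but it has little force against one. The completeness condition does no work for age, which will not be missing. At stake are precision and the credibility of the primary estimate should the arms differ visibly in age. The validity of the test is not at stake.

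**Working it through.** **Inputs from the Sample size section.** Difference 6.5 kPa, SD 9.0 kPa, two-sided alpha 0.05, power 80%, 1:1 allocation, 31 evaluable per group, about 10% attrition, 70 in total.

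**Inputs the documents do not give (assumptions, shown as ranges).**
- rho, the correlation of baseline with week-4 stiffness: 0 and 0.5.
- r, the partial correlation of age with week-4 stiffness given baseline: 0 to 0.4.

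**Step 1. Reproduce the plan's figure.** n per group = 2 × (1.960 + 0.842)² × 9.0² / 6.5² = 30.1, rounded up to 31. Then 31 / 0.9 = 34.4, rounded up to 35 per group, or 70. Both stated figures reproduce. At 31 per group a two-sample t-test has 79.9% power.

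**Step 2. Power of the ANCOVA.** With N = 62 and k covariates besides group:
- residual SD = 9.0 × sqrt(1 − rho²), multiplied by sqrt(1 − r²) when age is included;
- expected variance inflation from estimating the slopes = (N − 3)/(N − k − 3), which is 59/58 = 1.017 for baseline only and 59/57 = 1.035 with age;
- error degrees of freedom = N − 3 = 59 for baseline only and N − 4 = 58 with age;
- noncentrality = 6.5 / (residual SD × sqrt(2/31 × inflation)).

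Example at rho = 0: the noncentrality is 6.5 / (9.0 × sqrt(0.0645 × 1.017)) = 2.82, giving 79.2% power. With a useless age term it is 2.79, giving 78.5%.

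| | without age | r = 0 | r = 0.1 | r = 0.2 | r = 0.3 | r = 0.4 |
|---|---|---|---|---|---|---|
| rho = 0 | 79.2% | 78.5% | 78.9% | 80.1% | 82.2% | 85.1% |
| rho = 0.5 | 89.3% | 88.8% | 89.1% | 90.0% | 91.4% | 93.4% |

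The last digit can move by one with rounding.

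**Step 3. Cost and break-even.** If age is useless, the ratio of interval widths is (2.0017/2.0010) × sqrt(1.0351/1.0172) = 1.009, or 0.9% wider. Age repays that cost once r² exceeds 1 − 1/1.0091² = 0.018, so r of about 0.13. All four listed covariates, if useless, would widen the interval by about 3.8% and take power at rho = 0 from 79.2% to 76.2%.

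**Step 4. Chance imbalance.** The standardized age difference between arms has SD sqrt(2/31) = 0.254. A gap above 0.25 SD arises in about 32% of trials, and one above 0.5 SD in about 5%. If ages were uniform on 2–18 (an assumption), the SD of age is 16/sqrt(12) = 4.6 years, so the SD of the difference in mean age is 4.6 × 0.254, about 1.2 years. A gap of 0.5 SD shifts the estimate that omits age by r × residual SD given baseline × 0.5:
- r = 0.2: 0.2 × 9.0 × 0.5 = 0.90 kPa at rho = 0, or 0.78 kPa at rho = 0.5;
- r = 0.3: 1.35 kPa at rho = 0, or 1.17 kPa at rho = 0.5.

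The target difference is 6.5 kPa.

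**Step 5. Simulation check.** With 8,000 trials per setting and 31 per group, a useless age term gave power of 79.1% without and 78.4% with it (rho = 0), and 89.4% against 88.9% (rho = 0.5). Across the settings simulated, type I error was 4.3–5.0% without age and 4.5–5.0% with it.

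**The case against.** The strongest reply is that nothing here is an error. The protocol fixes one primary model, and baseline value of the outcome as sole covariate is a defensible choice with correct type I error. That stands. A reader might infer that omitting age biases the primary comparison, but the documents do not support this: randomization makes the estimate unbiased, and ordinary chance imbalance is already reflected in its confidence interval.

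The second reply is that no section relates age to week-4 stiffness once baseline is known, and baseline stiffness of the same muscle in the same child may carry most of any age effect. That also stands. The Introduction's remarks on developmental features, and the plan's own listing of age, make a relation plausible but do not establish one. Nor is the adjustment strictly free: below a partial correlation of about 0.13 it loses a little power.

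The third reply concerns the optional wording. A reader might infer that the analyst could pick the more favourable result. That goes too far. The adjusted model is supportive only, the prespecified ANCOVA remains the primary framework, analysts are to stay blinded until the main analysis is complete where possible, and a dated analysis plan is due before database lock. Firm wording for the supplementary model can be settled there.

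Finally, the absence of stratification is an inference from no factor being named.

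**Conclusion.** The point holds as a recommended improvement, not as a fault in the analysis. The worst case, an age term of no prognostic value, costs one degree of freedom, at most about 0.7 power points and an interval about 0.9% wider. The possible gain at 31 per arm is about 1 to 6 power points for partial correlations of 0.2 to 0.4 if baseline and week-4 stiffness are uncorrelated, and about 0.7 to 4 points if their correlation is 0.5. It also removes the linear effect of any chance age difference from the estimate. The size of the benefit rests entirely on the assumed partial correlation and on a roughly linear age effect. The cost figures do not depend on the size of that correlation.

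**What to change.** In the Statistical analysis section, and in the analysis plan still to be finalized, define the primary ANCOVA as week-4 affected-side stiffness on treatment group, baseline affected-side stiffness and age as one continuous linear term. Keep the baseline-only ANCOVA as a named sensitivity analysis, and check non-linearity in age only as a further sensitivity analysis. Leave sex, symptom duration and baseline pain in the supplementary model. Date the change and record it before anyone sees unblinded outcome data.

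The cost is wording and one error degree of freedom (59 to 58). No new data are collected, no child drops out of the primary analysis for missing age, and the target of 70 is unchanged.
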